#### Longitudinal study (secondary evaluation criteria C to E)

2.3.2

Six and 12 months after deliberation of the approved doctor’s opinion, a longitudinal analysis will enable the following secondary objectives to be met:C. Estimate the road risk prediction performance metrics of each assessment tool (cf. main objective) and of the TRIP, as well as of the approved doctor’s opinion;D. Explore participants’ changes in their driving habits;E. Explore the impact of educational support to encourage or dissuade driving resumption (only explored after 6 months).

##### Secondary criterion C: road risk performance metrics 6 and 12 months after deliberation of the approved doctor’s opinion

2.3.2.1

The predictive performance indicators of assessment tools, TRIP grid, and approved doctor’s opinion will be estimated in relation to the road risk perceived by participants 6 and 12 months after deliberation of the approved doctor’s opinion (cf. secondary criterion D). The patient will indicate the increase in road risk to road risk according to their perception, in the form of a ternary variable in response to the question “How would you assess your road risk”: (i) lower than before, (ii) identical to before, (iii) higher than before the brain injury. The condition evaluated will be absence of increased road risk perceived by participants 6 and 12 months after the approved doctor’s opinion (negative result), corresponding to the “favorable” modality for assessments carried out in rehabilitation centers (neuropsychological, RDA and multi-professional evaluation) and “fit” for the approved doctor’s opinion (Table 4).

**Table 4 tab4:** Confusion matrix.

		Reality: perceived increased road risk 6 and 12 months after the approved doctor’s opinion has been issued	
		No increased road risk	Increased road risk
Prediction: assessment x_i_	Favorable	Real negative (RN)	False negative (FN)
	Unfavorable	False positive (FP)	Real positive (RP)

The TRIP score will also be analyzed continuously (total adjusted score out of 100), in total and by sub-score.

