##### Patient feedback session

2.2.1.6

Professionals communicate the multiprofessional opinion to the participant, if possible in the presence of one or more relatives. They then provide the participant with documents required for the approved doctor visit: list of approved doctors, multiprofessional evaluation report, medical questionnaire, cerfa 14880*02 and, if necessary, a tutorial on completing formalities with the French National Agency for Secure Documents (Agence Nationale des Titres Sécurisés, ANTS).

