##### Approved doctor visit

2.2.1.7

Following the multiprofessional evaluation, participants then have to undergo a consultation with an approved doctor from their department. They then inform the study investigator of the opinion issued by the approved doctor (fitness, temporary fitness and/or with restriction(s), unfitness).

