#### Statistical analysis

2.3.3

To meet the main and secondary A and B objectives, concordance tests will be used to verify that two independent abilities to resume driving measures (two tests) of the same modality—“Favorable” or “Unfavorable”—are equal. Concordance analyses between tests (binary variables) will be expressed in the form of concordance percentages, simple kappa coefficient and its 95% confidence interval. Analyses between TRIP (continuous variable) and other tests (binary variables) will be conducted using *t*-tests or Mann–Whitney tests depending on the TRIP score distribution. Multivariate regression will also be used to study measures’ concordance and prediction levels, for both objectives. It will be logistic or linear, depending on the studied variable (i.e., approved doctor’s opinion for objective A and TRIP results for objective B).

A sensitivity and specificity analysis of the approved doctor’s opinion will also be carried out. Performance metrics (Secondary Objective C) will be calculated from the confusion matrix values (Table 4):$$\mathrm{Accuracy:}\frac{RP+RN}{RP+RN+FP+FN}$$$$\mathrm{Sensitivity (Se):}\frac{RP}{RP+FN\text{.}}$$$$\mathrm{Specificity (Sp):}\frac{RN}{FP+RN}$$$$\mathrm{Positive predictive value (PPV) or Precision (Pr):}\frac{RP}{RP+FP}$$$$\mathrm{Negative predictive value (NPV):}\frac{RN}{FN+RN}$$

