### Longitudinal study

3.2

Thanks to the longitudinal study, further analyses will enable us to measure the relevance of the multiprofessional evaluation by comparing each assessment with the road risk. Assessments that are significantly correlated with perceived road risk (as well as with self-reported accident rates) can be considered as good predictors of road risk, further supporting their relevance.

The longitudinal study will also shed light on any changes in driving habits adopted by participants since regularization of their driving license. These analyses will quantify the adoption of coping strategies related to npABI sequelae. Complementary analyses would also enable us to study relationships between changes in driving habits and various assessment scores. For example, a high correlation between changes in driving habits and BIDSAM would highlight the link between metacognition and behavioral regulation (adjusting driving to compensate for cognitive sequelae).

Lastly, this longitudinal study will provide some answers to the HAS recommendation that people with npABI be given the best possible support to resume or stop driving. By questioning participants, the support for resuming driving questionnaire will highlight the self-reported relevance of multiprofessional assessment for:- Judging their driving ability- Becoming aware of their driving ability- Obtaining information and advice from the team- Adjusting their driving (in the case of unrestricted fitness to drive)- Understanding the reasons for unfitness to drive or driving restrictions (in the case of fitness with restriction codes)- Dissuading them from driving (in the event of unfitness)

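### Criterion C scores the opinions against a self-rating made by participants who already know the main ones, so Table 4 measures agreement with a later perception, not prediction of road risk

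*Protocol article*

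**What the plan says.** The order of events is set out in the protocol article.

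- **Feedback (2.2.1.6).** "Professionals communicate the multiprofessional opinion to the participant, if possible in the presence of one or more relatives". The participant also receives the evaluation report to take to the approved doctor.
- **Doctor's opinion (2.2.1.7).** Participants see the approved doctor. "They then inform the study investigator of the opinion issued by the approved doctor", so they know it.
- **Reference (2.3.2.1).** The indicators for the center's assessments, the TRIP and the doctor's opinion "will be estimated in relation to the road risk perceived by participants 6 and 12 months after deliberation of the approved" doctor's opinion. At 6 and 12 months the same participant rates their own road risk as "i) lower than before, (ii) identical to before, (iii) higher than before the brain injury". Table 4 heads this column "Reality: perceived increased road risk 6 and 12 months after the approved doctor’s opinion has been issued".
- **Metrics (2.3.3).** "Performance metrics (Secondary Objective C) will be calculated from the confusion matrix values": accuracy, sensitivity, specificity and both predictive values.
- **Interpretation (3.2).** Assessments significantly correlated with perceived risk may be considered good predictors of road risk. Self-reported accident rates are added in parentheses.

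Accident rate and the DBQ are also collected at both follow-up times (2.2.2), but neither is the reference in Table 4. The limits in 3.3 do not mention that participants know the opinions.

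**The concern.** Estimating predictive accuracy requires a reference result that was not itself shaped by the test result. Here the person who supplies the reference has been told the result being tested, and has had 6 or 12 months to adopt it, reject it or change their driving because of it. Any of these links opinion and rating without the opinion having said anything true about risk.

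The protocol itself gives reasons to expect such a link. The support questionnaire asks whether the evaluation helped in "Becoming aware of their driving ability" (3.2), support is meant to encourage or dissuade driving (2.2.2), and an unfavorable or reserved opinion leads to proposals such as restrictions or alternatives to driving (2.2.1.8).

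At stake is what criterion C may conclude. Road-risk prediction is an aim stated in the abstract, 3.2 attaches the words good predictors to this result, and 3.4.2 foresees findings entering the training of approved doctors and possibly clarifying the decree.

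**Working it through.** The plan gives no target accuracy or expected figure for criterion C, so there is nothing to reproduce. The check uses Table 4 and the formulas in 2.3.3.

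**Inputs.** From the document: the table layout, the formulas and the planned 100 participants (2.1). Assumed, because the document gives no values:
- u = share with an unfavorable opinion (reserved counted as unfavorable)
- pU = probability of answering 'higher' after an unfavorable opinion
- pF = the same after a favorable opinion

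The opinion is set to be unrelated to true risk, so any gap between pU and pF comes only from knowing the opinion or reacting to it.

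**Formulas.** RP = u·pU; FP = u·(1−pU); FN = (1−u)·pF; RN = (1−u)·(1−pF). Se = RP/(RP+FN); Sp = RN/(RN+FP); J = Se + Sp − 1. An uninformative test gives J = 0 whatever its separate Se and Sp, so J is the quantity to watch.

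**Opinion has no effect on the rating** (u = 0.40, pU = pF = 0.15): RP 0.06, FP 0.34, FN 0.09, RN 0.51. Se = 0.06/0.15 = 0.40; Sp = 0.51/0.85 = 0.60; J = 0.

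**Participants adopt the opinion** (pU = 0.35, pF = 0.15): RP 0.14, FP 0.26, FN 0.09, RN 0.51. Se = 0.14/0.23 = 0.61; Sp = 0.51/0.77 = 0.66; J = 0.27.

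**Those told unfavorable drive less or stop, and rate their risk lower** (pU = 0.15, pF = 0.35): RP 0.06, FP 0.34, FN 0.21, RN 0.39. Se = 0.06/0.27 = 0.22; Sp = 0.39/0.73 = 0.53; J = −0.24.

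**Range over other assumed shares:**

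| u | pU | pF | Se | Sp | J |
|---|---|---|---|---|---|
| 0.40 | 0.25 | 0.15 | 0.53 | 0.63 | 0.16 |
| 0.40 | 0.45 | 0.15 | 0.67 | 0.70 | 0.37 |
| 0.30 | 0.35 | 0.25 | 0.38 | 0.73 | 0.10 |
| 0.50 | 0.50 | 0.20 | 0.71 | 0.62 | 0.33 |
| 0.30 | 0.20 | 0.40 | 0.18 | 0.64 | −0.19 |
| 0.50 | 0.20 | 0.40 | 0.33 | 0.43 | −0.24 |

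**Would it look like a finding?** Section 3.2 speaks of significant correlation but 2.3.3 names no test for criterion C. Taking a two-sided 5% comparison of two proportions as a stand-in, with all 100 followed up and u = 0.40, simulation gives significance in about 65% of studies for 35% versus 15%, about 26% for 25% versus 15%, and about 92% for 45% versus 15%. With no effect of the opinion it is about 5%. Loss to follow-up would lower the first three.

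**The case against.** Several points on the other side are sound.

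- **Direction.** A reader might infer that disclosure must inflate apparent accuracy. The documents do not support that. Stopping or restricting driving after an unfavorable opinion can honestly produce the answer 'lower', and J then turns negative.
- **Belief only.** A reader might also infer that the table would measure nothing but belief in the verdict. That is too strong: participants have months of further experience, and greater awareness could make some self-ratings more accurate. The support questionnaire item on awareness explores perceived usefulness; it is not a statement that the opinion will move the criterion C answer.
- **Ranking of tools.** It is tempting to say that disclosed opinions are favored over undisclosed results. Section 2.2.1.6 also hands over the evaluation report, which may carry the neuropsychological and on-road results, and participants experienced the drive themselves. Who knows what is uncertain, and criterion C specifies no ranking.
- **Other outcomes.** Accident rate is collected and named in 3.2, so perceived risk is not the only road-risk outcome.
- **Weight.** The criterion is secondary, the study exploratory, and the main concordance criterion is untouched. Disclosure is part of usual care and cannot be removed. Section 2.3.2.1 does say 'perceived' throughout.

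These points limit direction, scope and severity. They do not remove the dependence: the word 'perceived' sits beside the label 'Reality', the metrics in 2.3.3 are computed from that table alone, and 3.2 turns the result into a statement about road risk.

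**Conclusion.** The concern holds in a bounded form. The sequence of disclosure followed by self-rating is explicit, and nothing in the article separates the rating from knowledge of the opinions. Criterion C as laid out can therefore show performance different from chance, in either direction, for an opinion that says nothing about true risk. Under the assumed shares, J runs from about −0.24 to 0.37 where the correct value is 0. The existence of the dependence rests on the text; its size and sign rest on assumptions. It applies most directly to the multiprofessional and approved doctor's opinions, and less certainly to the neuropsychological and on-road opinions and the TRIP. Severity: moderate.

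**What to change.** 1. **Section 2.3.2.1 and Table 4:** replace 'Reality' with 'participant's later perceived road risk', and present accuracy, sensitivity, specificity and predictive values as agreement between the assessment and that perception, not as prediction of road risk.
2. **Section 2.3.2.1:** report each assessment also against the self-reported accident rate and, as supporting evidence, against the DBQ score at 6 and 12 months.
3. **Section 3.2:** do not call an assessment a good predictor of road risk, or compare assessments with one another, on perceived risk alone.
4. **Section 3.3:** list as a limit that participants knew the multiprofessional and doctor's opinions when they rated their risk.

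The cost is wording plus analyses of data already collected. The added outcomes are no full cure. Accidents are likely to be few among about 100 participants (the documents give no expected number), so estimates will be imprecise. Accident and DBQ data still come from the same informed participants, and the DBQ measures aberrant driving behavior rather than road risk, which is why it should support perceived risk and not simply replace it as the reference.

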##### Participant support

2.2.1.8

In the event of a favorable opinion, professionals help the participant with administrative formalities (ANTS website, road safety education office in the event of changes to the driving cab). In the event of an unfavorable or reserved opinion, professionals propose solutions to the participant (driving restrictions, rehabilitation in a simulator or driving school, time lapse before a new assessment, alternatives to driving, etc.).

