#### Longitudinal study

2.2.2

Six and 12 months after deliberation of the approved doctor’s opinion, the study investigators of the rehabilitation centers will send questionnaires to each participant of the cross-sectional study in order to study the road risk prediction performance of the tools and professional opinions. These questionnaires can also be completed with the help of a third party or a therapist. They will aim to gather information about participants’ driving in the 6 and 12 months since the opinion on fitness to drive was delivered. The elements investigated will concern:- aberrant driving behavior with DBQ validated in French (Guého et al., 2014),- possible changes in driving habits with DHQ, based on the Canadian Jerome Driving Questionnaire (JDQ©), and- road risk (accident rate and perceived risk).

Six months after the approved doctor’s opinion, participants will also be asked to complete a questionnaire (support for resuming driving questionnaire) to assess the relevance of multiprofessional educational support aimed at encouraging them to resume driving or dissuading them from doing so. In order to limit participant drop-outs, if they do not respond within one month, a reminder is sent by their SMR referent, with a one-month response period and this procedure will be repeated a second time if no response is received after this deadline. After these two reminders, the SMR referent may also contact the participant by phone to ensure that the e-mails have been received. If the participant refuses or does not reply, the SMR referent sends a final e-mail to the participant to inform them that they will be excluded from the longitudinal study.

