### Expected results

2.4

As this is an exploratory study, no assumptions are made concerning concordances between the different professional opinions. However, in light of the literature concerning coping strategies used by people with npABI, we can expect some results:

In the event of an unfavorable opinion on the neuropsychological assessment and a favorable opinion on RDA, we should observe high compensation scores on the TRIP, as well as a low score on the BIDSAM, indicating good metacognition enabling the driver to adapt their driving to their difficulties.

In the event of an unfavorable opinion on both the neuropsychological assessment and RDA, we should observe low compensation scores on the TRIP and a high score on the BIDSAM, indicating a low awareness of difficulties that does not allow the use of compensatory strategies.

TRIP compensation scores and the BIDSAM score should be good predictors of road risk.

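### Criterion C scores every assessment against the participant's own perceived change in risk, with no restriction to people who drive, so correct unfavorable opinions can be counted as false positives

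*Protocol article*

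**What the plan says.** Section 2.3.2.1 (Secondary criterion C) defines the reference as "The condition evaluated will be absence of increased road risk perceived by participants 6 and 12 months". It comes from a single question with three answers, "i) lower than before, (ii) identical to before, (iii) higher than before the brain injury". The column header of Table 4 reads "Reality: perceived increased road risk 6 and 12 months". An unfavorable opinion combined with no perceived increase is a false positive, and a favorable opinion combined with no perceived increase is a real negative. Section 2.3.3 computes accuracy, sensitivity, specificity, PPV and NPV from these cells.

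On who answers, section 2.2.2 states that the investigators "will send questionnaires to each participant of the cross-sectional study in order to study the road risk prediction performance". Section 3.2 lists follow-up content aimed at people found unfit, so they are among the intended respondents. After an unfavorable or reserved opinion, section 2.2.1.8 offers, among other options, "time lapse before a new assessment, alternatives to driving".

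On awareness, section 2.4 expects participants with unfavorable neuropsychological and on-road opinions to have a high BIDSAM score, "indicating a low awareness of difficulties that does not allow the use of compensatory strategies". It also expects BIDSAM to predict road risk.

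On other outcomes, section 2.2.2 collects the DBQ, the DHQ and "road risk (accident rate and perceived risk"). Section 3.2 would regard assessments correlated with perceived risk ("as well as with self-reported accident rates) can be considered as good predictors of road risk"). The Table 4 metrics use perceived risk only.

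**The concern.** Two features of the reference make it fail mainly where the assessment is unfavorable.

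The first is exposure. The opinion under test can stop a person from driving. Someone who no longer drives can truthfully say that their road risk is lower than before the injury, and none of the three answers described allows for not driving. Table 4 then charges that answer to the opinion as an error, although it is a consequence of the opinion.

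The second is awareness. The protocol's own expectation is that people with two unfavorable opinions are poorly aware of their difficulties, and such people are badly placed to report an increased risk. Any association of BIDSAM, an awareness measure, with perceived risk is confounded for the same reason.

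What is at stake is the reading of objective C. Section 3.2 would call assessments good predictors of road risk on this basis, and section 3.4.2 foresees using the study's results in the training of approved doctors and to clarify the decree.

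**Working it through.** The plan states no figure for criterion C, so there is nothing to reproduce. The check applies the formulas of section 2.3.3 to constructed tables. N = 100 is the planned total in section 2.1. Every other input is an assumption, because the document gives neither the share of unfavorable opinions nor the distribution of answers.

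**1. A perfect assessment.** Let U be the number with an unfavorable opinion, all truly at higher risk, and let s be the share of them who answer 'lower' or 'identical' because they are unaware or have stopped driving. Then RP = U(1 − s), FP = U·s, FN = 0 and RN = 100 − U. Scored against true risk, every metric is 1.00. Scored by Table 4:

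| U | s | RP | FP | RN | Specificity RN/(RN+FP) | PPV RP/(RP+FP) | Accuracy |
|---|---|---|---|---|---|---|---|
| 40 | 25% | 30 | 10 | 60 | 60/70 = 0.86 | 0.75 | 0.90 |
| 40 | 50% | 20 | 20 | 60 | 60/80 = 0.75 | 0.50 | 0.80 |
| 40 | 75% | 10 | 30 | 60 | 60/90 = 0.67 | 0.25 | 0.70 |
| 20 | 50% | 10 | 10 | 80 | 80/90 = 0.89 | 0.50 | 0.90 |
| 60 | 50% | 30 | 30 | 40 | 40/70 = 0.57 | 0.50 | 0.70 |

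PPV equals 1 − s in every row. Sensitivity stays at 1.00 because FN = 0.

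**2. When sensitivity moves.** Take a perfect assessment with 30 truly at risk, a share u of them unaware, and a share o of the 70 safe participants reporting an increase. Then RP = 30(1 − u), FP = 30u, FN = 70·o and RN = 70(1 − o).
- u = 50%, o = 20%: sensitivity 15/(15 + 14) = 0.52, specificity 56/(56 + 15) = 0.79.
- u = 50%, o = 0: sensitivity 15/15 = 1.00, specificity 70/(70 + 15) = 0.82.

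For a perfect assessment, the loss of sensitivity thus depends entirely on over-reporting by safe participants.

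**3. An imperfect assessment.** True cells: RP 30, FN 10, FP 10, RN 50, giving sensitivity 0.75, specificity 0.83, PPV 0.75, NPV 0.83.
- Half of the truly at-risk are unaware in both rows: RP 15, FN 5, FP 25, RN 55. Sensitivity is unchanged at 15/20 = 0.75, specificity is 55/80 = 0.69, PPV 15/40 = 0.38, NPV 55/60 = 0.92. Five real misses are now counted as real negatives, which raises NPV.
- Only half of the correctly flagged report no increase, as when they stopped driving: RP 15, FN 10, FP 25, RN 50. Specificity is 50/75 = 0.67, PPV 0.38, NPV unchanged at 50/60 = 0.83. Sensitivity falls to 15/25 = 0.60 because the misses still report an increase while half of the hits do not.

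**4. Non-drivers in or out of the table.** Assume 70 favorable (60 no increase, 10 increase), 10 unfavorable who drive (5 and 5) and 20 unfavorable who do not drive and answer 'lower'.
- All 100: specificity 60/85 = 71%, PPV 5/30 = 17%, accuracy 65/100 = 65%.
- The 80 drivers: specificity 60/65 = 92%, PPV 5/10 = 50%, accuracy 65/80 = 81%.
- Sensitivity (5/15 = 33%) and NPV (60/70 = 86%) are the same either way.

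**The case against.** The strongest reply is that the analysis set for criterion C is not written down. A mailing to every participant is not a Table 4 denominator. Section 2.3 allows some participants to be left out of certain analyses and foresees optional sub-groups by the conclusion of the medical examination, and the full protocol and case report form are not shown. This stands as a caveat: keeping non-drivers in the table is inferred. But the mailing is explicitly for studying prediction performance, the exclusion clause in section 2.3 concerns missing data, and neither provision is tied to criterion C.

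It is also fair that non-drivers need not answer 'lower'; someone just found unfit might answer 'higher'. Reserved opinions are initially classed as unfavorable (section 2.3.1.1), so that row may contain people who drive with restrictions. The mechanism is plausible and its frequency unknown.

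A reader might infer three stronger points that the document does not support:
- **The reference could reverse the ranking of two assessments.** Nothing here shows that: each table above scores a single tool.
- **Sensitivity must collapse.** For a perfect assessment it does so only under assumed over-reporting.
- **The BIDSAM expectation cannot be tested.** It can still be examined against accidents, which section 3.2 foresees relating to the assessments.

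Finally, section 2.3.2.1 says openly that the risk is perceived, even in the header beginning with 'Reality', so nothing is concealed.

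**Conclusion.** The point holds with these limits. As written, criterion C can score correct unfavorable opinions as false positives, through driving cessation and through unawareness, and can hide missed cases as real negatives. Specificity, PPV and accuracy can be too low for a correct assessment. NPV can be too high when unaware participants were given a favorable opinion. The bias runs in both directions, so the metrics cannot be read as conservative. The limits section (3.3) does not mention the issue.

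Its size cannot be derived from the document. The ranges shown rest on assumed shares of unfavorable opinions (20–60%) and of no-increase answers among them (25–75%), and on the inference that non-drivers stay in the table. The main criterion is unaffected. As this is a secondary criterion of a study described as exploratory, it should be fixed but does not undermine the study.

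**What to change.** In criterion C:

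1. Rename the Table 4 reference 'self-perceived road risk' in place of 'Reality', and do not conclude from it alone that an assessment predicts road risk. Align section 3.2 with this.
2. Report Table 4 for all respondents and again among those who report driving in the interval (from the DHQ), with the share not driving under each opinion.
3. Beside perceived risk, report the self-reported accident rate relative to driving exposure, and the DBQ score as a continuous outcome, as further reference outcomes.

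The data are already collected, so the cost is analysis wording and extra tables. The limitations should be stated with the results. The drivers-only table has a smaller denominator, may leave few people in the unfit row, and selects on a consequence of the opinion, which is why it should accompany the all-respondent table and not replace it. Accidents over 6 to 12 months in at most 100 people may be few. Accidents and the DBQ remain self-reported, and the document gives no DBQ cut-off, so neither should simply replace perceived risk as the single reference.
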